## Abstract

**Background::**

Advances in epidermal growth factor receptor-tyrosine kinase inhibitor (EGFR-TKI) treatment led to research on the mechanism of the resistance have revealed that an occurrence of T790M gene mutation generated in exon 20 of the EGFR gene is associated with approximately 50% to 60% of observed resistance. Osimertinib, a 3rd-generation EGFR-TKI, has been shown to be effective against both EGFR tyrosine kinase inhibitor-sensitizing and T790M resistance mutations. In this study, we prospectively investigate the efficacy and safety of osimertinib in elderly patients aged ≥75 years, with ineffective prior EGFR-TKI treatment or with recurrence of EGFR-TKI mutation-positive or T790M mutation-positive nonsmall-cell lung cancer.

**Patients and methods::**

In total, 35 subjects of both sexes aged ≥75 years with T790M mutation will be included. Participants with pulmonary disorders such as idiopathic pulmonary fibrosis, interstitial pneumonia, pneumoconiosis, active radiation pneumonitis, drug-induced pneumonia, and symptomatic brain metastasis will be excluded. Eligible patients will be administrated osimertinib (80 mg/d) until disease progression. The primary outcome is antitumor effect (objective response rate). The secondary outcomes are progression-free survival, overall survival, disease control rate, and safety.

**Ethics and dissemination::**

The protocol was approved by the institutional review boards of Kyoto Prefectural University of Medicine and all the participating hospitals. Written informed consent was obtained from all patients before registration, in accordance with the Declaration of Helsinki. Results of the study will be disseminated via publications in peer-reviewed journals.

**Trial registration::**

Trial registration number = UMIN000022553.

## Introduction

1

In recent years, advances in epidermal growth factor receptor-tyrosine kinase inhibitor (EGFR-TKI) treatment led to research on the mechanism of the resistance have revealed that an occurrence of T790M gene mutation generated in exon 20 of the EGFR gene is associated with approximately 50% to 60% of observed resistance.^[1]^

Afatinib, a 2nd-generation EGFR-TKI covalently linked in a tyrosine kinase domain of EGFR, is known to show a high antitumor effect by inhibiting phosphorylation irreversibly, and there was a report that showed a proliferation inhibitory effect on lung cancer cell strain that had T790M mutation^[2]^; therefore, therapeutic effects in patients with T790M mutation-positive lung cancer (T790M-positive patients) were initially expected. However, at present there has been no study in which a primary endpoint was achieved in a clinical trial for T790M-positive patients. Moreover, it is known that digestive organ toxicity and dermal toxicity of afatinib are strong, and as for the safety in the elderly, the medical evidence is not yet clear, unlike that for the 1st-generation EGFR-TKI.

Osimertinib is a 3rd-generation EGFR-TKI. Osimertinib has potential inhibitory effect on not only mutant form tyrosine kinase sensitive to 1st- and 2nd-generation EGFR-TKI, but also T790M mutant form EGFR tyrosine kinase, and has high selectivity for low inhibitory activity on wild-type EGFR tyrosine kinase.^[3]^ When the inhibitory activity on wild-type EGFR-TKI is high, toxicity such as rash and diarrhea is observed. Thus, it is thought that toxicity of osimertinib would be clearly favorable in comparison with conventional EGFR-TKI with low selectivity.

As evidence for the clinical effect relevant to osimertinib, based on the results of the AURA phase I study and the 2 AURA phase II studies, overall response rate (ORR) and duration of response (DoR) of osimertinib as 1st-line treatment was reported to be 75% (95% confidence interval [CI]: 62–85) and 18 months, respectively.^[4]^ In addition, in the 2 studies still in progress (AURA extension study and AURA2 study), superior efficacy was also reported in T790M-positive patients having treatment history.

In the AURA extension study, ORR was 61% (95% CI: 54–68) and median DoR and median progression-free survival (PFS) were not calculable (NC); and in AURA2 study, ORR, median DoR, and median PFS were 71% (95% CI: 64–77), 7.8 months (95% CI: 7.1 months to ∼NC months), and 8.6 months (95% CI: 8.3–9.7), respectively.^[5]^

The main adverse events reported in the group receiving 1st-line treatment in the AURA study, AURA extension study, and AURA2 study were rash (all grades: 77%, ≥grade 3: 2%; all grades: 40%, ≥grade 3: 1%; all grades: 42%, ≥grade 3: 1%) and diarrhea (all grades: 73%, ≥grade 3: 3%; all grades: 45%, ≥grade 3: 1%; all grades: 39%, ≥grade 3: 1%), respectively.^[4,5]^ These results suggest the possibility of relatively safe use of osimertinib with few serious adverse events for the elderly in comparison with conventional EGFR-TKI, while showing an antitumor effect for T790M-positive patients. However, it is difficult to show sufficient data for these estimations.

At this time, we are prospectively investigating the efficacy and safety of osimertinib for elderly patients ≥75 years old with ineffective prior EGFR-TKI treatment or with recurrence in EGFR-TKI mutation-positive and T790M mutation-positive nonsmall-cell lung cancer (NSCLC).

On the other hand, tolerance sometimes soon develops in patients in whom treatment with EGFR-TKI was effective, and it is said that about half of the tolerance is caused by the resistant mutation T790M. However, since histological tissue examination of lung cancer is more highly invasive than for cancers of other organs, there are many difficult cases of patients with exacerbation after treatment involving particularly frequent re-tests. The expression of T790M in plasma DNA using the highly sensitive polymerase chain reaction appears in a report to relate to resistant generation of EGFR-TKI, but there are still many questions about the concordance rate with tissue T790M. We are therefore prospectively investigating positive/negative concordance rate of T790M between tumor tissue or humoral specimen and plasma DNA in the present study.

### Endpoints

1.1

#### Primary

1.1.1

The primary endpoint is ORR.

#### Secondary

1.1.2

The secondary endpoints are PFS, overall survival (OS), disease control rate (DCR), safety, and positive/negative concordance rate of T790M between tumor tissue or humoral specimen and plasma DNA.

## Methods and analysis

2

### Study design

2.1

The study is single arm, open trial. Figure 1 depicts a flow chart of the study.

**Figure 1 F1:**
[figure not shown]
Study flow chart.

### Study setting

2.2

Forty-seven hospitals agreed to take part in this study. The protocol was approved by the institutional review board of each hospital. Written informed consent was obtained from all patients before registration, in accordance with the Declaration of Helsinki. Patients are registered in this study after independent review by the Data Center of the Clinical Research Support Centre Kyushu, where the potential subjects are screened against the inclusion and exclusion criteria. At least annual independent monitoring is planned, in accordance with the Japanese clinical trial guideline.

### Participants

2.3

The inclusion criteria are as follows:

(1)Patients with histologically or cytologically confirmed stage IIIB/IV NSCLC and postoperative recurrence.(2)Patients with recurrence after the effect of higher than stable disease (SD) or not effective (less than SD) was observed in best overall response according to RECIST by treatment of EGFR-TKI (e.g., such as erlotinib, gefitinib, afatinib) for NSCLC.(3)NSCLC harboring EGFR (activating) mutation and T790M positive.(4)Patients able to accept treatment with oral medicine.(5)Patients having at least 1 measurable lesion according to RECIST criteria.(6)Performance Status (ECOG) 0 to 1.(7)In principle, patients capable of participating this study for at least 2-week hospital stay or corresponding management.(8)Patients who are ≥75 years of age (at the time of enrollment).(9)Patients for whom bone marrow, hepatic, and renal functions have all been confirmed as normal within 14 days prior to enrollment according to the following clinical test standards:(1)white blood cell ≥ 3000/mm^3^ to ≤ 12,000/mm^3^(2)neutrophil count ≥ 1500/mm^3^(3)platelet count ≥ 100,000/mm^3^(4)hemoglobin ≥ 9.0 g/dL(5)aspartate aminotransferase, alanine aminotransferase ≤ 100 IU/L(6)total bilirubin ≤ 1.5 mg/dL(7)creatinine ≤ 2.0 mg/dL(8)SpO_2_ (Room air) ≥ 90%(10)Patients with life expectancy of at least 3 months.(11)Patients whose prior treatment has passed by the planned starting point of administration (eligible from the same day after past period).(1)Chemotherapy: ≥4 weeks have passed since the final treatment of prior chemotherapy(2)EGFR-TKI: the next day after the last administration(3)Radiation therapy in the case of chest: ≥12 weeks have passed since the day of final radiation treatment(4)In the case of radiation to other than chest: ≥2 weeks have passed since the day of final radiation treatment(5)Operation/treatment (including chest drainage): ≥4 weeks have passed since the day of final operation/treatment(12)Patients who provide written informed consent to participate in the study

The exclusion criteria are as follows:

(1)Patients who have treatment history of osimertinib or other 3rd-generation EGFR-TKI.(2)Patients with pulmonary disorders such as idiopathic pulmonary fibrosis, interstitial pneumonia, pneumoconiosis, active radiation pneumonitis, and drug-induced pneumonia.(3)Patients with infectious disorder requiring intravenous injection of antibacterial drugs or antimycotics.(4)Patients unable to swallow oral medications.(5)Patients currently receiving (or unable to stop use prior to receiving the first dose of study treatment) medications or herbal supplements known to be potent inhibitors of CYP3A4 (at least 1 week prior) and potent inducers of CYP3A4 (at least 3 weeks prior). All patients must avoid concomitant use of any medications, herbal supplements, and/or ingestion of foods with known inducer/inhibitory effects on CYP3A4.(6)Patients currently receiving checkpoint inhibitor.(7)Patients with any of the following cardiac criteria:(1)Mean resting corrected QT interval (QTc using Fridericia formula) >470 ms.(2)Any clinically important abnormalities in rhythm, conduction, or morphology of resting ECG (e.g., complete left-bundle branch block, 3rd-degree heart block, 2nd-degree heart block).(3)Any factors that increase the risk of QTc prolongation or risk of arrhythmic events such as heart failure, hypokalemia, congenital long QT syndrome, family history of long QT syndrome, or unexplained sudden death under 40 years of age in 1st-degree relatives or any concomitant medication known to prolong the QT interval.(8)Patients who are pregnant, nursing, or possibly pregnant.(9)Patients with symptomatic brain metastasi.(10)Patients with active double cancer.(11)Patients with uncontrollable diabetes mellitus.(12)Patients who have complications of clinical concern.(Such as uncontrollable cardiac disease, severe cardiac arrhythmia requiring medical treatment, sustained serious diarrhea.)(13)Any other patients who are regarded as unsuitable for this study by the investigators.

### Dose and treatment regimens

2.4

Osimertinib 80 mg OD tablet is orally administered. Oral administration of osimertinib is continued until progressive disease or the criteria for discontinuation.

### Rationale for the setting of the number of enrolled subjects

2.5

From data of the 2 AURA phase II studies (AURA extension study and AURA2 study) in EGFR-T790M mutation-positive patients, ORR was reported to be 61% (95% CI: 54–68) in the AURA extension study (n = 201), and ORR and median PFS were reported to be 71% (95% CI: 64–77) and 8.6 months (95% CI: 8.3–9.7) in AURA2 study (n = 210), respectively.^[4,5]^ In addition, regarding docetaxel, assumed the standard treatment in elderly patients in Japanese guidelines, ORR of docetaxel was reported to be 22.7% in a controlled study with vinorelbine and 41.2% in a study of combined administration of carboplatin and pemetrexed in elderly Japanese patients.^[6,7]^ The expected response rate and threshold response rate are determined to be 60% and 35%, respectively. Under these conditions, when a 2-sided significance level of 5% and a test power of 80% are assumed, 31 subjects are required. Considering allowance for dropouts, 35 subjects were planned.

### Statistical methods

2.6

ORR: response rate and its 2-sided 95% CI (Wilson method). When the lower limit of the estimated CI exceeds a threshold of 35%, statistical significance is decided.

PFS: survival curve, median (Kaplan–Meier method), CI of the median (Brookmeyer and Crowley method), standard error of the annual rate (Greenwood method).

OS: survival curve, median (Kaplan–Meier method), CI of the median (Brookmeyer and Crowley method), standard error of the annual rate (Greenwood method).

DCR: disease control rate and its 2-sided 95% CI (Wilson method).

Concordance rate of T790M: sensitivity, specificity, positive predictive value, negative predictive value, accuracy, and kappa coefficient.

Safety: grade and frequency of each adverse event.

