### Population to be analyzed

2.7

All subjects enrolled in this study (full analysis set [FAS]); the subjects excluding the patients with serious violations (such as serious protocol deviation, violation for inclusion/exclusion criteria, and violation for prohibited concomitant medication/therapy) from FAS (per protocol set); and among the FAS in which the protocol treatment is provided at least once (safety analysis set).

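### The article plans specificity, NPV, kappa and a negative concordance rate for T790M but names no population containing T790M-negative patients; in enrolled patients, judged on their qualifying specimens, these cannot be estimated

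*Protocol article*

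**What the plan says.** - **Endpoint.** Protocol article, section 1.1.2, lists among the secondary endpoints the "positive/negative concordance rate of T790M between tumor tissue or humoral specimen and plasma DNA". The Introduction gives the same aim and places it within this trial: "We are therefore prospectively investigating positive/negative concordance rate of T790M between tumor tissue or humoral specimen and plasma DNA in the present study".
- **Statistics.** Section 2.6 specifies "Concordance rate of T790M: sensitivity, specificity, positive predictive value, negative predictive value, accuracy, and kappa coefficient".
- **Eligibility.** Inclusion criterion 3 in section 2.3 is "NSCLC harboring EGFR (activating) mutation and T790M positive". It does not say which specimen establishes positivity. The Abstract agrees on who is enrolled: "In total, 35 subjects of both sexes aged ≥75 years with T790M mutation will be included".
- **Populations.** Section 2.7 defines the full analysis set as everyone enrolled. The per protocol and safety sets are subsets of it. The text describes no set of screened or T790M-negative patients.

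**The concern.** Specificity, NPV, kappa and negative concordance all need patients who can be negative. The only patients the article says will be analysed were selected for being positive. Selection on one of the two tests being compared, or on either of them, empties part of the 2×2 table before any data are collected.

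At stake is a named secondary aim. The Introduction justifies the comparison by the difficulty of repeat tissue sampling and by doubts about how well plasma matches tissue. A kappa of 0 or below, or an NPV of 0%, would look like a verdict on the plasma assay when it only reflects who was enrolled. Section 2.9 reports 34 subjects enrolled by April 2018 against a plan of 35, so further recruitment under the same criteria would not supply negatives.

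**Working it through.** **The plan's own figure.** The article gives no number for the concordance analysis. Its one computed figure is the 31 subjects for response rate (section 2.5: 35% versus 60%, two-sided 5%, power 80%). The arcsine formula gives [(1.960 + 0.842) / (2(arcsin√0.60 − arcsin√0.35))]² = 30.65, so 31. That reproduces and has no bearing on this point.

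**Notation.** Tissue or fluid is the reference. Let a = both positive, b = plasma only, c = tissue/fluid only, d = both negative, and n = a + b + c + d.

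- Sensitivity = a/(a+c); specificity = d/(b+d)
- PPV = a/(a+b); NPV = d/(c+d)
- Accuracy = po = (a+d)/n
- pe = [(a+b)(a+c) + (c+d)(b+d)]/n²; kappa = (po − pe)/(1 − pe)

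**Step 1: the three possible entry routes**, assuming enrolled patients are analysed on the specimens that qualified them.

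| Entry by | Empty cells | Sensitivity | Specificity | PPV | NPV | Accuracy | Kappa |
|---|---|---|---|---|---|---|---|
| Tissue/fluid | b, d | a/n | 0/0 | 100%* | 0%* | a/n | 0* |
| Plasma | c, d | 100%* | 0%* | a/n | 0/0 | a/n | 0* |
| Either | d | a/(a+c) | 0%* | a/(a+b) | 0%* | a/n | ≤ 0* |

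*Where defined. Under tissue/fluid entry with every plasma result positive, for example, NPV and kappa are both 0/0.

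**Step 2: why kappa cannot be positive here.** With d = 0, po = a/n and pe = [(a+b)(a+c) + bc]/n² = (an + 2bc)/n². So po − pe = −2bc/n², which is 0 if b or c is 0 and negative otherwise. Listing every possible table at n = 35 (36 for tissue/fluid entry, 36 for plasma entry, 666 for either) confirms a maximum kappa of 0. At n = 34 the pattern is the same.

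**Step 3: examples (assumed counts).**

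- Tissue/fluid entry, 21 of 35 plasma-positive (21, 0, 14, 0): sensitivity 0.60, accuracy 0.60, PPV 1, NPV 0/14 = 0, specificity 0/0, kappa 0.
- Same route, 28 of 35 plasma-positive: sensitivity 0.80, but kappa is still 0.
- Either-specimen entry (20, 5, 10, 0): po = 20/35 = 0.571; pe = (25×30 + 10×5)/1225 = 0.653; kappa = −0.0816/0.3469 = −0.235. PPV here is 20/25 = 80%, so it is not fixed.

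**Step 4: the same assay with negatives included.** Keep a = 21 and c = 14, and add 35 tissue-negative patients, so b + d = 35. Then pe = 0.5 and kappa = 2(21 + d)/70 − 1 = (d − 14)/35. The documents give no specificity, so a range is shown:

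| Assumed specificity | d | Kappa |
|---|---|---|
| 80% | 28 | 0.40 |
| 86% | 30 | 0.46 |
| 100% | 35 | 0.60 |

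At d = 30, NPV is 30/44 = 0.68. Sensitivity is 60% in every row, as in the first example of Step 3. The kappa of 0 there comes from selection, not from the assay.

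**The case against.** The strongest reply is that the article condenses a fuller protocol. Section 2.7 does not tie any of its sets to the concordance endpoint, section 2.2 says candidates are screened before registration, and the flow chart cannot be seen. Paired results from screened patients may exist, and an endpoint that names both positive and negative concordance would suit such a group. This stands as a limit: a reader might infer that the trial has no T790M-negative comparison group at all, but the article neither describes nor excludes one. What can be said is that it names no population that supports these statistics.

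Second, a reader might infer that kappa can never exceed 0 in this trial. That holds only if the compared specimens are the qualifying ones. Criterion 3 gives neither specimen nor date. If other specimens were compared, both-negative pairs could occur and kappa could be positive.

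Third, it is tempting to call every listed statistic undefined or fixed. Accuracy is not: it can take values from 0 to 1, although it says nothing about negatives, and it merely repeats sensitivity under tissue/fluid entry or PPV under plasma entry. PPV is fixed at 100% only under tissue/fluid entry, and sensitivity at 100% only under plasma entry. Striking out PPV whatever the entry route would therefore be unsound.

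None of this rescues the text as printed. Leaving the qualifying specimen unstated does not help, because the both-negative cell is empty under all three routes.

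**Conclusion.** The point holds in conditional form. If enrolled patients are analysed on the specimens that established eligibility, specificity and NPV are 0 or undefined and kappa is at most 0 or undefined, so negative concordance cannot be estimated. This is more than detail left to an analysis plan: the article lists statistics that the only population it defines cannot supply. The size of the distortion depends on unknown counts. In the illustration, an assay with 60% sensitivity shows kappa 0 instead of 0.40 to 0.60.

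The conclusion rests on two assumptions: no tested screening cohort is used, and the qualifying and compared specimens are the same.

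A reader might rank this as a must-fix. The endpoint is secondary, with no test or sample size attached, and the response-rate rule, survival and safety analyses are untouched. It is a should-fix.

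**What to change.** 1. In 2.3, state which specimen establishes T790M positivity. In 2.6, state the population and specimens for the concordance analysis.
2. If paired tissue/fluid and plasma results already exist for all screened patients regardless of T790M result, name that screened set as the concordance population and keep the listed statistics.
3. Otherwise, delete specificity, NPV and kappa from 2.6, and the negative part of the endpoint from 2.6 and 1.1.2. Report only what the entry route identifies, with a Wilson 95% CI:
   - tissue/fluid entry: positive percent agreement, meaning the plasma-positive share of tissue/fluid-positive patients (for an assumed 25 of 35, 71%, CI 55% to 84%);
   - plasma entry: PPV;
   - either-specimen entry: both, provided both specimens were tested in all patients.

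The cost is a wording change to one secondary endpoint and its analysis. Under option 3 the negative-concordance claim is given up.

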### Population to be analyzed

2.7

All subjects enrolled in this study (full analysis set [FAS]); the subjects excluding the patients with serious violations (such as serious protocol deviation, violation for inclusion/exclusion criteria, and violation for prohibited concomitant medication/therapy) from FAS (per protocol set); and among the FAS in which the protocol treatment is provided at least once (safety analysis set).

### Ethics

2.8

The trial received ethical approval from the Ethics Committee of Kyoto Prefectural University of Medicine, Kyoto, Japan (number: ERB-C-630-3, the last edition ver 3. December 21, 2016). The trial is subject to the supervision and management of the Ethics Committee.

### Trial status

2.9

This study opened to recruitment in March 2016, with a planned last follow up in October 2019. As of April 2018, 34 subjects have been enrolled.

## Discussion

3

It is now well established that acquisition of a second mutation in EGFR, resulting in substitution of threonine at the “gatekeeper” amino acid 790 to methionine (T790M), is the most common resistance mechanism. Second-generation irreversible EGFR-TKIs such as afatinib are effective in untreated EGFR-mutant lung cancer. However, as monotherapy, they have failed to overcome T790M-mediated resistance in patients, because concentrations at which these irreversible TKIs overcome T790M activity preclinically are not achievable in humans due to dose-limiting toxicity related to nonselective inhibition of wild-type EGFR. This situation has led to the development of “3rd-generation” EGFR-TKIs that are designed to target T790M and EGFR-TKI-sensitizing mutations more selectively than wild-type EGFR. Osimertinib has been shown to be effective against both EGFR tyrosine kinase inhibitor-sensitizing and T790M resistance mutations. On the other hand, an increase in life expectancy in the general population has led to a rise in the incidence of lung cancer in elderly patients. In the United States, almost half (47%) of all lung cancer patients are more than 70 years old, and 14% are more than 80 years old. By the same token, in Japan, the number of elderly patients diagnosed with lung cancer is increasing, with almost half of all Japanese patients with NSCLC reported as 75 years of age or older. We therefore need to evaluate efficacy and safety in elderly patients.
